## **4.2 INCLUSION CRITERIA**

- Aged 18 – 70 years
- Male or female
- Diagnosed with AI for over 6 months according to standard diagnostic criteria
- Established on stable HC replacement or prednisolone replacement, dose not altered for at least 3 months
- Established on a stable dose of Fludrocortisone, if taking, dose not altered for at least 3 months
- Participants taking other hormone replacements (e.g. levothyroxine, testosterone or growth hormone in secondary adrenal insufficiency) are accepted providing that their replacement doses have not altered for at least 3 months
- Participants who are otherwise healthy enough to participate, as determined by pre-study medical history and physical examination.
- Participants who are able and willing to give written informed consent to participate in the study.

## **4.3 EXCLUSION CRITERIA**

- Participants with a diagnosis of Type 1 or Type 2 diabetes mellitus.
- Unable to give informed consent.

## Safety and Efficacy of Prednisolone in Adrenal Insufficiency Disease (PRED-AID Study) Protocol

- Taking supplements or herbal medications that the participant is unwilling or unable to stop prior to and during the study period e.g. St John's Wort (may decrease prednisolone levels), Cat's claw, Echinacea (immunomodulatory properties).
- Currently taking medications that alter CYP3A4 metabolism of glucocorticoids that the participant is unwilling or unable to stop prior to and during the study period e.g. phenytoin, phenobarbital, rifampicin, rifabutin, carbamazepine, primidone, aminoglutethimide, itraconazole, ketoconazole, ciclosporin or ritonavir.
- Pregnancy, taking the combined oral contraceptive pill, or oral oestrogen replacement therapy due to the effects on cortisol binding globulin levels and determination of prednisolone levels. Transdermal oestrogen replacement is permitted.
- Diagnosis of congenital adrenal hyperplasia, untreated

#### 4.4 WITHDRAWAL CRITERIA

Participants will be free to withdraw from this study at any time without prejudicing any further treatment. Participants will also be withdrawn from the study if they lose the capacity to consent. If participants experience any significant AEs, they may be withdrawn following a review by the Chief Investigator.

Upon withdrawal, participants will be returned to their baseline steroid replacement therapy, which may be titrated by a study clinician if necessary. They will continue to be followed-up by their direct care team at their usual endocrinology outpatient clinic.

Following withdrawal, samples and data previously collected by study team will continue to be held and may be used in the data analysis phase. Participants will be informed of this at the time of obtaining consent.

It is understood by all concerned that an excessive rate of withdrawals can render the study uninterpretable; therefore, unnecessary withdrawal of patients should be avoided. Should a participant decide to withdraw from the trial, all efforts will be made to report the reason for withdrawal as thoroughly as possible and they will be encouraged to continue to provide follow-up data for the remaining trial visits for the current treatment period.

## 5. RANDOMISATION AND ENROLMENT PROCEDURE

### 5.1 RANDOMISATION OR REGISTRATION PRACTICALITIES

Randomisation will be managed through the Oracle InForm data capture system. This is a validated GCP-compliant data capture and management system. The allocation to study arm will be based on the original randomisation list populated and held by an independent statistician at the ICTU, which will be available for reference and back-up if the InForm database is unavailable.

Participant demographic data will be uploaded to the InForm system at enrolment, when they will be assigned a Study ID. Participants who successfully complete the two-week dose finding period (if required) will then be randomised to a study arm, receiving a Study Drug ID based on their blocking factor. The Imperial pharmacy will be made aware of the allocation and will dispense the appropriate blinded study medication and specified placebo at the patient's individual dose, for the relevant study period.

## 5.2 UNBLINDING

This is a double-blind study. The randomisation lists and/or code break envelopes will be held by:

1. Pharmacy at the ICHNT (randomisation spreadsheet)
2. [name] - administrator in the department of Investigative Medicine
3. [name], General Manager, NIHR Clinical Research Facility, in a secure area within the centre
4. [name], Quality Assurance and Governance Manager, NIHR Clinical Research Facility, in a secure area within the centre
5. [name] unblinded co-investigator

In the case of a medical emergency or in the event of a serious medical condition, when knowledge of treatment allocation is essential for the clinical management or welfare of the participant, an investigator or other physician managing the subject may decide to unblind that subject's treatment code. They should therefore request and obtain the relevant code-break envelope from [name] or her designated deputy if she is away. Alternatively, [name] can be contacted via the Imperial College Healthcare NHS Trust switchboard and will also be in possession of the relevant code-break envelope.

The investigator must sign and date the open unblinding envelope, as soon as is reasonably possible. Within 24 hours of the code break, the reason for the code break must be documented on the envelope. The Investigator will also record the date and reason for revealing the blinded treatment assignment for that subject in the CRF and in the subject's medical notes. The sponsor should also be notified.

## 6. TREATMENTS

### 6.1 TREATMENT ARMS

This is a two-arm, two-period crossover study. Participants will be randomly assigned to either arm (A) or arm (B), which will dictate the order in which the two alternative treatments are administered (Appendix 2):

A) Participants given once daily low dose prednisolone (at 2-5 mg, determined by the serum level of prednisolone at 8 hours after a test dose) with placebo tablets at lunch and in the afternoon for four months (first period); followed by hydrocortisone once daily or multiple doses daily (at their stable therapeutic regimen or the dose identified

## Safety and Efficacy of Prednisolone in Adrenal Insufficiency Disease (PRED-AID Study) Protocol

post-screening, anticipated to be 10mg, 5mg, 5mg for most participants) for four months in the second period

B) Participants given hydrocortisone once daily or multiple doses daily (at their stable therapeutic regimen or the dose identified post-screening, anticipated to be 10mg, 5mg, 5mg for most participants) for four months (first period); followed by given once daily low dose prednisolone (at 2-5 mg, determined by the serum level of prednisolone at 8 hours after a test dose) with placebo tablets at lunch and in the afternoon for four months in the second period

Both study periods in each arm will last for 4 months. In-between study periods, there will be a minimum 2-week washout period, during which participants will return to their pre-study baseline treatment.

After a participant has completed the study periods, they will return to their baseline treatment.

All study specific medication will be administered via the oral route. To ensure the integrity of the double-blinded study design, all the medication and placebos will be bulk produced by Activase Pharmaceuticals Ltd, who will be providing the medications free of charge. The bulk material will be sent to the Tiofarma who will bottle and label the medication.

The medication will be dispensed by the ICHNT pharmacy who will be responsible for ensuring that the participants randomised to each study arm receive their study medication in the correct order corresponding to the study period.

It is anticipated that the study medication will be delivered to the ICHNT pharmacy in bulk and will be dispensed according to the need of each individual participant. The excess stock of tablets will be held by Tiofarma and will be delivered to ICHNT pharmacy if their stocks are running low.

## 6.2 DOSE MODIFICATIONS FOR TOXICITY

Dose modifications for toxicity will not be required in this study. Participants will already be accustomed to one of the two treatments in this study, as they will have been using the medication at the same dose for at least 3 months prior to enrolling onto the study.

If a participant is naïve to the alternative steroid medication, they will be given a trial of at least 2-weeks prior to randomisation. During this time, the dose of the alternative medication will be titrated, according to the standard clinical practices used at ICHNT.

## 6.3 PREMEDICATION

Vitamin D levels will be checked in each participant at screening. All participants will be required to demonstrate replete vitamin D levels (>40 nmol/L) during the trial as low vitamin D levels directly influence the concentration of bone markers such as osteocalcin. Participants with low vitamin D levels at screening (<40 nmol/L) are anticipated to receive a dose of 20,000 units for a period of 6 weeks before starting the study. Specific vitamin D replacement regimens may vary and some participants may have repeat vitamin D measurements but this will be assessed on a case by case basis, depending on the clinical picture. The final decision regarding vitamin D replacement regimens will lie with the Chief Investigator.

During the study all participants will be prescribed 800 – 1000 units daily for the duration of the trial, as is expected in standard care. Any deviation from this regimen will be decided upon on a case-by-case basis according to clinical requirement and agreed with the Chief Investigator.

#### **6.4 INTERACTION WITH OTHER DRUGS**

Participant require steroid replacement therapy to manage their medical condition for the rest of their lives. This should not impede them from taking other medications if indicated.

#### **6.5 DISPENSING AND ACCOUNTABILITY**

All the medication and placebos will be produced as bulk material by Activase Pharmaceuticals Ltd, who will be providing the medications free of charge. The bulk material will be sent to Tiofarma who will bottle and label the medication. QP release will be done by Tiofarma.

The medication doses required by each participant will be individual and determined according to the participant's previous experience with the medication, or else the outcome of the dose-finding period if the participant has not previously used one of the study medications. At randomisation, the participant will be given a Study Drug ID, allocated according to the blocking factor. The clinician will notify the pharmacy of the dose of hydrocortisone, and prednisolone needed by the participant and the sizes of placebo to be dispensed when the participant is on the prednisolone treatment period.

The medication will be dispensed by the ICHNT pharmacy who will be responsible for ensuring that the participants randomised to each study arm receive their study medication in the correct order corresponding to the study period, as dictated by their Study Drug ID, which will be cross-checked against the randomisation list.

At times of intercurrent illness, participants will have the autonomy to double their steroid dose. This is performed independently as part of their usual care. They will be asked to inform a study physician at any time they double their doses.

Individual patients have their own routines as to how they double their steroids. A common routine is for the participant to double their steroid dose for a minimum of three days, or else as long as the period of intercurrent illness. After the illness has resolved, the participant will usually reduce their steroid dose back to the usual regimen.

In practice during this study, participants will double their steroid dose by taking double the tablets that they usually administer from each bottle. Therefore if a participant takes one tablet from the morning bottle, one from the noon bottle, and one from the evening bottle, they will instead take two from each bottle. The only exception to this will be when they take their first dose of doubled steroids.

For the first doubled dose, participants will be asked to take their usual tablet, but to double their first dose with a tablet from the morning bottle. This is necessary as participants who need to double their dose from noon or afternoon may be in the prednisolone study period. As such, doubling their dose at noon would mean that they have taken a double dose of placebo. The only way to overcome this problem, is to ask the first dose to be doubled with a morning tablet, which will contain active ingredient regardless of the study period.

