### 3. STUDY DESIGN

Patients with stably treated primary or secondary hypoadrenalism on either hydrocortisone or prednisolone replacement will be recruited to this study from patients attending endocrinology clinics in the UK.

This study will be a phase 3, two-period, randomised cross-over, double-blind study with two treatment arms:

A) Participants given once daily low dose prednisolone (at 2-5 mg, determined by the serum level of prednisolone at 8 hours after a test dose) with placebo tablets at lunch and in the afternoon for four months (first period); followed by hydrocortisone once daily, or multiple doses daily (at their stable therapeutic regimen or the dose identified post-screening) for four months in the second period

B) Participants given hydrocortisone once times daily, or multiple doses daily (at their stable therapeutic regimen or the dose identified post-screening) for four months (first period); followed by given once daily low dose prednisolone (at 2-5 mg, determined by the serum level of prednisolone at 8 hours after a test dose) with placebo tablets at lunch and in the afternoon for four months in the second period

Participants will be randomly assigned to begin with either treatment arm. Each treatment period will be continued for 4 consecutive months. Participants will then undergo a washout period during which they will be returned to their baseline treatment for a minimum period of 2 weeks, before starting on the alternate treatment arm. The aim is to assess the effect of each treatment arm on bone health, surrogate markers of cardiovascular risk, glycaemic control, infection rates, immunology profiles, patient wellbeing and compliance.

Participant randomisation will be blocked to ensure that equal numbers of patients receive the treatments in the two orders. Each block will be randomised according the type of AI (primary vs secondary).

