#### **6. DESIGN**

##### **6.1 STUDY DESIGN**

This study will be a phase 3, two-period, randomised cross-over, double-blind study with two treatment arms:

A) Participants given once daily low dose prednisolone (at 2-5 mg, determined by the serum level of prednisolone at 8 hours after a test dose) with placebo tablets at lunch and in the afternoon for four months (first period); followed by hydrocortisone three times daily (at their stable therapeutic regimen or the dose identified post-screening) for four months in the second period

B) Participants given hydrocortisone three times daily (at their stable therapeutic regimen or the dose identified post-screening) for four months (first period); followed by given once daily low dose prednisolone (at 2-5 mg, determined by the serum level of prednisolone at 8 hours after a test dose) with placebo tablets at lunch and in the afternoon for four months in the second period

PRED-AID Study Statistical Analysis Plan (SAP)

Participants will be randomly assigned to begin with either treatment arm. Each treatment period will be continued for 4 consecutive months. Participants will then undergo a washout period during which they will be returned to their baseline treatment for a period of 2 weeks, before starting on the alternate treatment arm. The aim is to assess the effect of each treatment arm on bone health, surrogate markers of cardiovascular risk, glycaemic control, infection rates, immunology profiles, patient wellbeing and compliance. A schematic of the Study Visits, timeline and study events to be undertaken can be found in Appendix 1.

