## 6.6 BLINDING

This is a double-blind study. To achieve sufficient blinding, patients will receive an individual tablet specially made for this study to be taken at their usual dosing times. Whilst taking hydrocortisone, patients will receive a hydrocortisone tablet in the morning, at noon, and in the afternoon, at their appropriate respective doses. When on prednisolone, patients will receive a single prednisolone tablet in the morning, at the appropriate dose. They will then receive placebo tablets at noon and in the afternoon.

In the case of a medical emergency or in the event of a serious medical condition, when knowledge of treatment allocation is essential for the clinical management or welfare of the participant, an investigator or other physician managing the subject may decide to unblind that subject's treatment code.

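### As written, the tablet scheme keeps the blind only for participants on three hydrocortisone doses a day, although the protocol permits other regimens

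*Combined protocol and SAP*

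**What the plan says.** **Hydrocortisone period, protocol.** Section 3 describes arm A as prednisolone "followed by hydrocortisone once daily, or multiple doses daily". Section 6.1 says the same for arm B: "Participants given hydrocortisone once daily or multiple doses daily (at their stable therapeutic regimen or the dose identified". It anticipates 10 mg, 5 mg and 5 mg for most participants, not all. The Study Summary also allows once-daily or multiple dosing.

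**Prednisolone period, protocol.** Sections 3 and 6.1 give one active dose "with placebo tablets at lunch and in the afternoon for four months".

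**Placebo supply, protocol.** Under section 6.5 the clinician tells the pharmacy the two active doses and "the sizes of placebo to be dispensed when the participant is on the prednisolone treatment period". The dose-doubling text in the same section also links placebo to that period: it explains that "participants who need to double their dose from noon or afternoon may be in the prednisolone study period", where a doubled tablet would be placebo.

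**SAP.** Section 6.1 has arm A "followed by hydrocortisone three times daily", and section 6.6 states: "Whilst taking hydrocortisone, patients will receive a hydrocortisone tablet in the morning, at noon, and in the afternoon".

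**Reason for the schedule.** Protocol section 1.2 says that people used to once-daily prednisolone must take extra tablets on a three-times-daily pattern, because the double blind needs it.

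**The concern.** The blind rests on tablets that look the same and on a tablet pattern that does not change between periods. The first is stated (protocol Appendix 2). The second holds only if the hydrocortisone regimen happens to have three doses.

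Participants know their own hydrocortisone regimen, either from established use or from dose-finding. Someone on once-daily hydrocortisone who is handed three bottles can infer prednisolone; one bottle points to hydrocortisone.

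SF-36, Addi-QoL, GNCQ and symptom reports are self-reported and compared within the same person, so knowing the treatment in both periods bears directly on that contrast. SAP section 7.2 excludes unblinded participants from the per-protocol set, but neither document plans to ask participants whether they have identified their treatment, so such cases could go unnoticed.

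**Working it through.** The plan gives no figure on this point to reproduce. The check sets the two periods side by side and counts tablets.

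**Inputs**
- Hydrocortisone doses per day, k: one or more, with no stated upper limit (protocol sections 3 and 6.1).
- Prednisolone-period tablets per day: 1 active + 2 placebo = 3 (protocol sections 3 and 6.1, Appendix 2).
- Placebo in the hydrocortisone period: none described.
- Tablets per dose: assumed to be one. SAP section 6.6 describes an individual tablet made for the study at each dosing time.
- Days on blinded treatment: Day 2 to Day 120 (protocol section 8), so 120 − 2 + 1 = 119 days per period.

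**Counts as written**

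Hydrocortisone period: k tablets a day, 119 × k in total. Prednisolone period: 3 a day, 119 × 3 = 357 in total.

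| Hydrocortisone doses a day (k) | Tablets a day, hydrocortisone v prednisolone | Tablets per period | Ratio, prednisolone to hydrocortisone |
|---|---|---|---|
| 1 | 1 v 3 | 119 v 357 | 3.00 |
| 2 | 2 v 3 | 238 v 357 | 1.50 |
| 3 | 3 v 3 | 357 v 357 | 1.00 |
| 4 | 4 v 3 | 476 v 357 | 0.75 |

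Only k = 3 matches. SAP section 6.6 describes exactly that row. The protocol also permits the others.

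**Missed doses.** SAP section 9.6.8 compares the number of missed doses between periods with a paired t-test or a Wilcoxon test. It compares counts and does not scale them to the tablets due. With the same chance of missing any one tablet, a once-daily hydrocortisone participant would be expected to miss three times as many in the prednisolone period (357 ÷ 119 = 3), with no real difference in adherence.

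**Number affected.** The documents give no split by regimen. Purely as illustration, 10% of 55 is 5.5 (about 6 people) and 40% of 55 is 22. Neither percentage comes from the documents.

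**Sample size.** Nothing changes. The SD of the within-person difference is 3.0 × √(2 × (1 − 0.5)) = 3.0. With 44 completers and a 1.5 µg/L effect, power is 90.0% (noncentral t, 43 df), as stated, and 44 ÷ 0.80 = 55.

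**The case against.** The strongest reply is that the gap is one of documentation and that the trial may in practice run a uniform schedule.
- No text forbids placebo in the hydrocortisone period. Protocol section 5.1 has the pharmacy dispense the specified placebo for the relevant period without naming which.
- The doubling instructions in protocol sections 1.2 and 6.5 speak of morning, noon and later-day bottles without reference to drug.
- Appendix 2 lists the same three times for both periods, although its doses are an example.
- Pharmacy manuals and bottling specifications are not among the documents.

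This stands to the extent that a reader who infers that these participants are in fact unblinded goes further than the text allows. The lack of hydrocortisone-period placebo is inferred from silence together with period-specific wording.

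It does not remove the point. The placebo that the clinician is told to specify is for the prednisolone period, and following that instruction literally gives unequal counts for regimens the protocol permits. The SAP avoids the problem only by assuming a frequency that the protocol does not require.

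The numbers are probably small. Protocol section 1.1 calls thrice-daily hydrocortisone the most common pattern, section 4.1 starts those not established on hydrocortisone on three doses, and section 6.1 anticipates three doses for most. Those exposed would mainly be people already established on another frequency.

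**Conclusion.** The point holds for the documents as written. They do not say how the blind is kept for any hydrocortisone regimen other than three doses a day, and the protocol and SAP contradict each other on frequency. If the stated dispensing text is followed, and each dose is one tablet, affected participants would see 1 v 3, 2 v 3 or 4 v 3 tablets a day and could identify the treatment. This is worth correcting, but it does not threaten the main conclusion.

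Three stronger readings are not supported:
- That the trial is unblinded. The number affected is not given and is probably a minority; the 6 to 22 people above are illustrative, not an estimate.
- That the patient-reported results are biased. They could be, in a subset; neither direction nor size can be shown from the documents.
- That the primary result is compromised. Day 120 osteocalcin is a laboratory measure and is less exposed.

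The unequal number of opportunities to miss a dose is a matter of counting. It needs no assumption about how participants behave once they guess the treatment, but it does rest on the same reading of the dispensing text.

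**What to change.** 1. In protocol sections 6.1 and 6.5 and SAP section 6.6, state that each participant has the same number of bottles, tablets and tablet times in both periods, with matching placebo in either period at any time that carries no active tablet. Word this for every permitted regimen. A rule of three bottles for everyone would not cover more than three doses, and the protocol sets no upper limit.
2. Check that the dose-doubling text in protocol sections 1.2 and 6.5 still works under that scheme, since it relies on which bottle holds active drug.
3. Reconcile the hydrocortisone-frequency wording in the protocol (Study Summary, sections 3 and 6.1) with SAP sections 6.1 and 6.6. Which frequency applies is for the sponsor.

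Equal counts also put the missed-dose comparison in SAP section 9.6.8 on the same footing in both periods.

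Active doses are unchanged. The cost is wording changes and extra placebo tablets for some participants, using a product already made for the trial; the documents give no stock or price figures. If the pharmacy already matches bottles, only the wording needs to change.
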